### Fidelity Analysis

Healthcare professional-reported fidelity checklists will be summarised descriptively to determine average adherence to the intervention, specific intervention components delivered and reasons for non-adherence.

Approximately 20% of audio recorded ENRICH review sessions will be selected to rate for in-depth fidelity of ENRICH intervention components (table 2). The research team will evaluate fidelity at critical time windows (eg, when conducting early reviews following training; after having conducted several ENRICH reviews) and prespecify recorded sessions to be evaluated for fidelity based on purposive sampling on psychological profiling (ensuring a range of severity, and whether fidelity varies based on patient profile). Recordings will be listened to by the research team and scored for presence of key components described above as well as quality of delivery. The research team will additionally evaluate proportion of time spent on intervention factors (eg, the content of the ENRICH reviews) versus factors unrelated to ENRICH (eg, social conversation).

### Study Progression Criteria

A priori defined progression criteria (table 4) will be used to determine whether the intervention can proceed to testing effectiveness in a cluster randomised controlled trial. These criteria were selected based on feasibility objectives, clinical assumptions and pragmatic expectations. If we do not meet targets in green, indicating that modifications are needed prior to progressing to an effectiveness trial, we will identify potential modifications from interview data described above with stroke participants, carers and healthcare professionals involved in ENRICH and agree on suitable modifications with the ENRICH advisory and PCPI committees. Final modifications will be discussed with the ENRICH advisory committee.

**Table 4 T4:** Progression criteria for ENRICH to a future effectiveness trial

Evaluation domain	Evaluation criterion	Green Proceed to trial	Amber Proceed to trial after modifications	Red Do not proceed to trial
Feasibility	Site recruitment	Two sites recruited within 6 months of REC approval.	Two sites recruited in more than 6 months since REC approval.	Unable to recruit sites.
	HCP recruitment	>50% of HCPs trained consented.	25%–50% of HCPs trained consented.	Less than 25% HCPs trained consented.
	Patients who had a stroke recruitment	Average >5 patients recruited per month.	Average 3–5 patients recruited per month.	<3 patients recruited per month by a site.
	Family member recruitment	>30% of recruited participants will have a family member who consent to provide outcome data.	10%–30% of recruited patients have a family member who consent to provide outcome data.	<10% of recruited patients have a family member who consent to provide outcome data.
Acceptability	ENRICH intervention delivery	≥50% of participants complete >1 ENRICH review.	30%–50% of participants complete >1 ENRICH review.	<30% of participants complete >1 ENRICH review.
	Outcome measure completion	≥75% completion of primary outcome measures (≥75%).	Moderate rates of completion of primary outcome measures (≥50%–75%).	Low rates of completion of primary outcome measures (<50%).
	Patients who had a stroke acceptability	Average rating of >3.5 out of 5 for helpfulness of ENRICH reviews.	Average rating of 3 out of 5 for helpfulness of ENRICH reviews.	Average rating less than 3 out of 5 for helpfulness of ENRICH reviews.
	Intervention delivery	Qualitative data supports feasibility with minor modifications.	Qualitative data supports feasibility but with major modifications made.	Qualitative data does not support feasibility, even with major modifications.
Fidelity	Treatment fidelity	≥70% adherence ratings across sites.	50%–70% treatment fidelity across sites.	Less than 50% treatment fidelity across sites.

ENRICH, ENhanced Reviews of PsychologIcal Changes; HCP, Health Care Professional; REC, Research Ethics Committee.

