## Methods and analysis

### Design

The ENRICH feasibility study is a single arm multicentre feasibility study across two sites, delivered at the site/cluster level, capturing detailed quantitative and qualitative data on feasibility, acceptability and fidelity focused primarily on the ENRICH intervention itself, aimed at informing the design of a future pragmatic cluster randomised controlled trial. We considered a site to be at least one NHS stroke service comprising the full stroke care pathway from acute to 6 months post-stroke. Where this comprised two separate services, this was considered one site for the purposes of delivering the ENRICH intervention.

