### Quantitative Data for Uncertainties in Study Design

With regards to study design, quantitative data on number of sites meeting initial site eligibility and numbers of expressions of interest will be collected. Per site, participant eligibility rates (defined as percentage of patients per site meeting study eligibility criteria), recruitment rates (total number of patients recruited per month across both informed and consultee advised consent), intervention completion (total number of ENRICH reviews received) and outcome completion rates for patients who had a stroke, carers (T2 assessment completion rates) and healthcare professionals (interview completion) will be collected.

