### Sample Size

No formal sample size calculation was conducted. As the primary aim is to evaluate feasibility, we aimed to recruit up to 80 stroke survivors across sites (an average of 40 participants per site), allowing for 25% attrition. These numbers are in line with UK averages on sample sizes for feasibility studies.^30^ Assuming 50%–60% of stroke survivors will have a carer/family member who can take part we further aimed to recruit 45 carers (N=45 target), and 15 healthcare professionals. There are no planned interim analyses.

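### Table 4 ties the red band for patient recruitment to a single site but gives no unit for green and amber, so green or amber can coincide with red and no rule says which prevails

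*Protocol article*

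**What the plan says.** The relevant row of Table 4 (Study Progression Criteria) has three cells:

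- Green, proceed to trial: "Average >5 patients recruited per month".
- Amber, proceed after modifications: "Average 3–5 patients recruited per month".
- Red, do not proceed: fewer than 3 "patients recruited per month by a site".

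Only the red cell names a site, and only the green and amber cells speak of an average. The text around the table gives no order of precedence between colours.

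Other sections bear on the unit:

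- Design describes a "single arm multicentre feasibility study across two sites".
- Quantitative Data for Uncertainties in Study Design lists, among the items gathered for each site, "recruitment rates (total number of patients recruited per month across both informed and consultee advised consent").
- Quantitative Analysis promises monthly recruitment numbers without saying whether they are per site or combined.
- Sample Size aims for "up to 80 stroke survivors across sites (an average of 40 participants per site), allowing for 25% attrition".

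**The concern.** Progression criteria are useful because they are fixed before the results are known and give one answer for any result. This row does not. Its outer bands carry opposite decisions, and red is measured on a different basis from the other two, or at least is worded as if it were. Uneven recruitment between two sites is an ordinary outcome, so a conflict of colours is a realistic prospect.

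Recruitment is part of the study's primary outcome (Primary Outcome), and the article presents the table as set a priori. If the row can return two colours, the choice between them is made after the recruitment figures have been seen. That is the choice the table was meant to remove.

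**Working it through.** **Inputs.** Two sites (Design). Bands of more than 5, 3 to 5, and fewer than 3 per month (Table 4). Target of up to 80 patients (Sample Size). Let *a* and *b* be the monthly rates at the two sites.

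**The plan's own figure.** 80 / 2 = 40 per site, which agrees with "an average of 40 participants per site". There is no formal sample size calculation to reproduce.

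**Reading 1: the average is the mean per site, (a + b)/2, and red means any site below 3.**

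- Sites at 9 and 2: (9 + 2)/2 = 5.5, green. The second site is at 2, red.
- Sites at 6 and 2: (6 + 2)/2 = 4, amber. The second site is at 2, red.
- In general, green with one site below 3 requires a + b > 10 with b < 3, so the other site must exceed 7. Amber with red needs much less imbalance.

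**Reading 2: the average is the two-site total, a + b, and red means any site below 3.**

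- Sites at 2.8 and 2.8: 2.8 + 2.8 = 5.6, green. Both sites are below 3, red.
- Sites at 3 and 2: 3 + 2 = 5, amber. One site is at 2, red.
- In general, the slower site is at most (a + b)/2. A total of 5 or less puts it at 5/2 = 2.5 or less, so every amber result is also red and amber can never apply alone. Likewise, any total below 6 puts the slower site below 3, so green between 5 and 6 is always also red.

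**Reading 3: all three bands are the mean per site.** The bands meet at 3 and 5 and do not overlap. There is no conflict, but the red cell would have to be read as an average, which it does not say.

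**Reading 4: all three bands are the two-site total.** Again there is no conflict, but the words tying red to a site would then be wrong.

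**How far apart the units are.** At the green boundary of 5 per month, 80 patients take 80/5 = 16 months on the total and 80/(2 × 5) = 8 months per site, a factor of 2. The article gives no recruitment window, so this shows how much the meaning of the threshold changes. It does not show that recruitment would fail.

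**The case against.** The best defence is that the row was meant as an average per site throughout. The section on study-design uncertainties collects recruitment rates site by site, and the cut-points meet exactly at 3 and 5, as bands on one scale should. On that reading, two sites at 2.8 are simply red. This is a reasonable guess at the intention, but the table does not say it. The red cell drops the word average and can equally mean any one site, and Quantitative Analysis names no unit. The fidelity row of the same table does say that its ratings are across sites, so the authors state the unit where they choose to.

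Two stronger readings are tempting, and the documents support neither.

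- A reader might infer that green and amber are definitely pooled over both sites. The article does not say so, and the per-site data collection leans the other way.
- A reader might infer that one dataset can be green, amber and red at once. On any single scale, more than 5 and 3 to 5 exclude each other. Sites at 4 and 2 show three colours only if the total (6, green) and the mean per site (3.0, amber) are both used, alongside the site at 2 (red).

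It is also fair to say that the consequences are limited. The study is descriptive, site-level rates will be available in any case, and the text sends missed green targets to the advisory and patient and public involvement committees to agree modifications. That softens red in practice, but the column heading still says not to proceed.

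**Conclusion.** The point holds in this form: the recruitment row does not use one unit, so green or amber can coincide with red, and no rule resolves the conflict. Under Reading 1 the conflict arises only when the sites recruit unevenly. Under Reading 2 it covers the whole amber band and the part of green below 6 per month.

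Both results assume two sites and that the red cell means any one site. If red was meant as an average on the same scale as the other two cells, the bands are sound and only the wording needs correcting.

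The defect lies in a published decision threshold, so it is not a detail that can be left to an analysis plan. Severity is moderate. It affects one of nine progression rows in a feasibility study, and no estimate or test depends on it.

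**What to change.** State one unit in all three cells.

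- Average patients recruited per site per month fits the way the rates are collected and makes the bands contiguous and mutually exclusive.
- If the two-site total was meant, delete the reference to a site in the red cell and say that both sites are combined.

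State in advance which colour applies when one site is below 3 but the average is not. The rule is the sponsor's to choose. If it gives anything milder than red, it relaxes the red cell as it can now be read, and should be acknowledged as a change. Report each site's rate beside the summary figure.

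The wording should be settled before recruitment rates are judged against the table. If that moment has passed, report the colour under each reading.

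The cost is a few words in Table 4. No new data are needed, because rates are already collected by site. The downside is that the colour may be less favourable than under the two-site total.

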### Quantitative Data for Uncertainties in Intervention Delivery

Our quantitative aims with regards to the delivery of the intervention are to investigate the numbers of trained clinicians delivering ENRICH reviews, proportions of recruited patients receiving ENRICH reviews and ratings of perceived helpfulness and usefulness (assessed using a custom Likert scale from 1 to 5) of ENRICH from healthcare professionals, patients who had a stroke and carers.

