### Qualitative Analysis

Results from the post-study survey will be summarised to determine whether patients who had a stroke and carers found the enhanced reviews helpful, relevant and whether information needs regarding post-stroke psychological needs were sufficiently met. We will similarly describe average ratings of helpfulness of ENRICH reviews from recruited healthcare professionals. Any changes required prior to the progression of a definitive trial based on acceptability data will be reported.

Qualitative data will be analysed using a framework analysis based on the Theoretical Framework of Acceptability (TFA^31^). The aim of the qualitative analysis will be to understand why and in what specific circumstances the intervention did or did not work and to identify potential ways to improve the intervention as a means of informing intervention acceptability. The research team will meet regularly throughout the transcription process to revise the analytical framework. Once all transcripts are coded, data will be charted in a framework matrix with candidate codes and participant quotes labelled by identification number, mapped against TFA components of affective attitude, burden, perceived effectiveness, ethicality, intervention coherence, opportunity costs and self-efficacy. The research team will reflect on the matrix and adapt it to represent other units of analysis (eg, clinicians vs participants, participants with cognitive impairment vs participants without cognitive impairment) to develop an understanding of intergroup similarities and differences in intervention perceptions across TFA domains. A final theme structure will then be constructed from the matrices that describes key barriers and facilitators to intervention delivery and potential modifications, if any, to be made for a future trial. In combination with helpfulness and usefulness ratings from participants, we will define acceptability as average helpfulness and usefulness ratings of at least 3.5 out of 5 on our custom survey and a smaller number of barriers reported in our framework analysis compared with perceived intervention benefits from patients who had a stroke and carers.

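### Table 4 gives no colour to mean helpfulness ratings above 3 and up to 3.5, and its acceptability row does not match the definition of acceptability under Qualitative Analysis

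*Protocol article*

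**What the plan says.** Two places in the protocol article set a rule for acceptability.

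Under Study Progression Criteria, the Table 4 row for acceptability to patients has three cells:
- green: "Average rating of >3.5 out of 5 for helpfulness of ENRICH reviews"
- amber: "Average rating of 3 out of 5 for helpfulness of ENRICH reviews"
- red: "Average rating less than 3 out of 5 for helpfulness of ENRICH reviews"

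The text above the table adds a general statement for all rows: "If we do not meet targets in green, indicating that modifications are needed prior to progressing to an effectiveness trial". The team then draws modifications from the interviews and agrees them with the advisory and public involvement committees.

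Under Qualitative Analysis, the rule is: "we will define acceptability as average helpfulness and usefulness ratings of at least 3.5 out of 5 on our custom survey". A second condition is attached: "a smaller number of barriers reported in our framework analysis compared with perceived intervention benefits from patients who had a stroke and carers".

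Helpfulness and usefulness are both rated from 1 to 5, by healthcare professionals, patients and carers (Quantitative Data for Uncertainties in Intervention Delivery).

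**The concern.** A traffic-light rule has to assign every possible result to one colour. In this row amber is one point on a continuous scale, and the interval between it and green is left blank. The other rows graded by a percentage or a monthly rate give amber a range, so this cell looks like a slip in drafting.

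The row and the text also measure different things. The text requires two ratings and includes 3.5; the row uses one rating and excludes 3.5. The row covers patients only, while the text brings in carers without saying whether their ratings enter the average.

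Acceptability is the first aim listed under Design, and Table 4 is presented as fixed in advance. If a middling mean is observed, its colour would have to be decided with the result in view. The report could also call ENRICH acceptable under one rule while the other says something else.

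**Working it through.** The article states no calculation for this criterion and reports that no formal sample size calculation was done, so there is no figure to reproduce. The check has three parts.

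**1. Which means have a colour?** The Sample Size section says: "we aimed to recruit up to 80 stroke survivors across sites (an average of 40 participants per site), allowing for 25% attrition". That gives 80 × 0.75 = 60 patients with a survey rating, assuming that every retained patient answers. The mean of 60 whole-number ratings from 1 to 5 is S/60, where S runs from 60 to 300, giving 241 attainable values.

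| Printed rule | Sums S | Number of means |
|---|---|---|
| Red, below 3 | 60 to 179 | 120 |
| Amber, exactly 3 | 180 | 1 |
| No colour, above 3 and up to 3.5 | 181 to 210 | 30 |
| Green, above 3.5 | 211 to 300 | 90 |

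The gap needs no assumption about the ratings. The number of respondents changes only how many attainable values fall in it.

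**2. How likely is an uncoloured mean?** The article gives neither an SD nor an expected rating. I assume an SD of 1.0, with 0.8 to 1.2 as the range. At SD 1.0 the standard error is 1/√60 = 0.129. With a half-unit correction h = 0.5/60 = 0.0083 and true mean μ, the normal approximation is

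P(no colour) = Φ((3.5 + h − μ)/SE) − Φ((3 + h − μ)/SE).

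For μ = 3.25 this is Φ(2.00) − Φ(−1.87) = 0.977 − 0.031 = 0.947.

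| True mean | P(no colour), SD 1.0 | SD 0.8 | SD 1.2 |
|---|---|---|---|
| 2.75 | 0.023 | 0.006 | 0.048 |
| 3.0 | 0.474 | 0.468 | 0.478 |
| 3.25 | 0.947 | 0.984 | 0.893 |
| 3.5 | 0.526 | 0.532 | 0.521 |
| 3.75 | 0.031 | 0.010 | 0.059 |
| 4.0 | 0.000 | 0.000 | 0.001 |

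Without the half-unit correction the figure at 3.5 is 0.50. The chance of landing exactly on amber is greatest at a true mean of 3.0, where it is 0.051 (0.043 to 0.064 over the SD range).

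**3. Where do the two rules disagree?**
- *Mean of exactly 3.5.* Acceptable on that rating in the text, not green in the table. At n = 60 this is one attainable mean, with a chance of 0.051 at SD 1.0 (0.043 to 0.064) even if the true mean is 3.5.
- *Helpfulness above 3.5, usefulness below 3.5.* Green in the row, not acceptable in the text. For example, helpfulness 3.8 with usefulness 3.0 is green in the row. It fails the text if each rating must reach 3.5, which is the natural reading. It also fails if the two are pooled, since (3.8 + 3.0)/2 = 3.4. The article gives nothing from which to put a probability on this case, but it is not confined to one point on the scale.

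**The case against.** The strongest reply is that nothing is really undecided. A mean of 3.2 is not green, and the printed limit of 3 means that it is not red, so only amber remains. The sentence on missing green also says what follows: modifications. This largely stands. A reader might infer that a middling result is unclassifiable, or that it could end in a decision not to proceed. The article does not support that, because amber can be inferred. What remains is that the inference is not printed, and the sentence does not print it either: it covers every result short of green, including those in the column that says not to proceed. Reading the amber 3 as a rounded figure does not help, since means from 2.5 to below 3 would then be both amber and red.

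A second reply is that a progression row may be narrower than an overall definition, and that the numerical clash arises only at exactly 3.5. The clash at 3.5 is indeed small. But the row carries the acceptability label, shares the 3.5 cut-off and leaves out usefulness without explanation, so the difference in what is measured stands.

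A third reply is that the high probabilities arise only when the true mean lies in or at the edge of the gap. That is correct: at 3.75 the chance is about 3%, and at 4.0 almost nil. The article gives no ground for expecting a middling mean.

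A reader might also infer that counting barriers against benefits leaves progression open to trivial benefits outvoting one serious barrier. The article does not support this. The count is not in Table 4, and the table has a separate qualitative row graded by whether minor or major modifications are needed, or whether even major ones would not suffice. That criticism is not part of this point.

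**Conclusion.** The criterion is wrong as written and should be fixed. The row leaves means above 3 and up to 3.5 without a stated colour, and it departs from the article's own definition in its boundary and in the ratings used. Both facts rest on the text alone.

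The practical size depends on the unknown true mean. With 60 respondents and an SD of 1, an uncoloured result is very likely near 3.25, about an even chance at 3.0 or 3.5, and unlikely from 3.75 upwards.

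It is not a fatal defect. The likely intent can be recovered, the study's primary outcome is feasibility (recruitment, attendance and completion of measures), and the quantitative analysis is descriptive, so no test depends on this cut-off.

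**What to change.** Make these changes before any ratings are seen:

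1. In the Table 4 row, print contiguous bands: green at least 3.5, amber 3.0 to below 3.5, red below 3.0. At n = 60 every attainable mean then has exactly one colour (120 red, 30 amber, 91 green), and 3.5 is treated as in Qualitative Analysis.
2. Apply the bands to both helpfulness and usefulness, with green requiring at least 3.5 on each, as the definition does. Add a line saying which colour applies when the two ratings fall in different bands below green. The article does not settle this, so the choice is for the authors.
3. State in both places whether carers' ratings count.

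The cost is wording only, since both ratings are already collected from patients and carers. The one downside is that green becomes slightly harder to reach once usefulness must also pass; moving 3.5 itself into green offsets this by a single attainable mean.
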